### Ethical approval and informed consent

This research has been authorized by the Ethical Committee of Clinical Research of Galicia and informed consent will be solicited from participants in the study, wherein the information sheet will explain the voluntary nature of collaborating and the participant's freedom to change procedures without giving any explanation. Thus, the confidentiality of both the participation and the information collected is ensured by its anonymous handling.

The study will observe basic ethical principles and the provisions of the law at all times.

### Phases of study

A working calendar of some 12 months was established for performing the study as such, followed by data analysis and dissemination of results.

In Phase 1 (first quarter), the main objective was to publicize the project and arouse interest so as to enable us to achieve a high degree of participation. Those interested were provided with detailed information on the process and the conditions.

The Family and Community Medicine teaching units throughout Galicia were contacted to invite tutors and residents to participate in the study. Participation was promoted by a drawing for a PDA and laptop computer among participants.

To ensure that participation in the study proceeds within a formal framework, each participant was sent a letter from the lead researcher in the project, along with an informed consent letter to be signed. A second letter was to be sent by the coordinator of field work, providing more specific details on the process and the phases of the study.

Based on the first version of the survey, the first phase included a review that will involve the participation of both experts and physicians, which might ensure that the wording of the questions was suitable. At the same time, all the materials necessary were prepared for the execution of the following phases.

The tutor-resident pair was assigned to each group-intervention or control-by simple random sample.

In Phase 2 (second quarter), a first use was made of the SOPS. This phase must was completed by both the control and intervention groups.

In Phase 3 (third quarter), an intervention was made in one of the groups pursuant to the protocol set forth above. In the control group, no action was taken.

In Phase 4 (fourth quarter), participants in both the control and intervention groups were again be provided with the SOPS to be filled out. The time between the two uses of the questionnaire was 4 months, an interval considered suitable, as it is too large for individuals to remember the answers given in the first phase and, at the same time, sufficient for the effect of the intervention to have been instilled and materialized in the daily work of medical professionals.

Phase 5 (third semester) was consist of a review of all the questionnaires, their encoding and recording in computer format and a statistical analysis of the data.

Finally, Phase 6 (fourth semester), at present, is the dissemination phase, with production of publications and presentation of results in the participating health centers.

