#### Population

Tutors belonging to the seven Family and Community Medicine teaching units of Galicia and residents in the last year of studies (MIR-4) of Family and Community Medicine.

In 2009, there were 160 tutors and 288 residents, of which 69 are MIR-4. As these residents and their tutors constitute the so-called "tutor-resident pair", we will request the participation of 35 tutors and 35 residents in the intervention group and 34 tutors and 34 residents in the control group.

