#### Randomization

Every tutor-resident pair in Galicia will be invited to participate. Tutor-resident pairs will be assigned randomly to experimental groups (control vs. intervention) through use of the SPSS 17 statistical package, by one team researcher not belonging to Primary Care. The pair will be assigned randomly to groups by stratifying the teaching unit to ensure their equivalence in relation to a number of variables of interest and to avoid possible underlying biases. Special care will be taken that both the intervention group and the control group will be comprised of the same number of individuals and that their distribution by health centers and areas will be also similar.

Twenty-four tutor-resident units in each group are required to detect an improvement in patient safety culture of 30% with 80% power and confidence level of 95%. If we estimate 10% in losses, 27 tutor-resident units per group must be captured.

Although the sample size calculated was 27, it was decided to invite the total population for three reasons: 1) Being an educational intervention, by the very execution of the survey (SOPS), and a research project at the same time. 2) In each of the 7 teaching units, a pair-resident tutor would be excluded, a priori; while statistically defensible, it would not be so from an organizational perspective, working environment, and the like. 3) Exactly match the sample size for efficiency and ethics of the study is not applicable in this case.

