### Data analysis

For the first hypothesis:

• Descriptive data analysis with traditional univariate character tabulation with central trend measurement and variability.

• Comparisons between groups and phases, with use of parametric bivariate contrasts (t of Student and simple variance analysis) and non-parametric ones (Wilcoxon and Kruskal Wallis).

• To measure the possible effect of the intervention and possible interaction, a variance analysis of repeated measurements will be used.

For the second hypothesis:

• Analysis of scale psychometric properties. To study the dimensionality or factor structure, an exploratory factorial analysis will be made, using the principal components method. To analyze reliability, indicators will be collected for internal consistency (Cronbach's α) and to study the criteria or predictive validity, an analysis of correlations and a multiple linear regression analysis will be made.

Finally, a descriptive analysis of declared adverse events will be undertaken

All analyses will be made with the SPSS 17 statistical package. Statistical significance will be assigned to p values lower than 0.05.

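### The article gives two incompatible allocation methods, stratified by teaching unit and simple random, and only the first can deliver the balance it claims

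*Protocol article*

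**What the plan says.** **Method.** Under Randomization, the article assigns pairs with SPSS 17, by a researcher from outside primary care: "The pair will be assigned randomly to groups by stratifying the teaching unit to ensure their equivalence". It adds that care will be taken that "both the intervention group and the control group will be comprised of the same number of individuals", and that the distribution over health centres and areas will be similar. Under Phases of study, the last step of Phase 1 reads: "The tutor-resident pair was assigned to each group-intervention or control-by simple random sample". No strata are mentioned there.

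**Numbers.** The Population section gives the planned arms as "35 tutors and 35 residents in the intervention group and 34 tutors and 34 residents in the control group", that is 69 pairs, drawn from seven teaching units. The size of each unit is not given.

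**Order.** Assignment falls in Phase 1, the first quarter. Then: "In Phase 2 (second quarter), a first use was made of the SOPS". The next sentence reads: "This phase must was completed by both the control and intervention groups". The arms therefore existed on paper when the baseline was collected.

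**Use of the baseline.** Under Data analysis: "To measure the possible effect of the intervention and possible interaction, a variance analysis of repeated measurements will be used".

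**The concern.** The allocation rule is a basic design fact, and here it is stated twice, differently. Stratification is the article's stated means of making the groups equivalent and of avoiding underlying bias. A simple random draw leaves the split within each unit to chance. The article's Background describes safety culture as something that the staff of a health centre hold in common, so the unit where a pair works is a plausible predictor of its score. A unit that falls mostly into one arm then adds noise to the comparison of the arms. The right analysis also depends on the answer: if unit was a stratum, the model should contain it.

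The order of events raises a second, weaker question. The SOPS is self-reported, and the control group receives no action, so participants cannot be kept unaware of their arm once the workshops begin. If they already knew it when they filled in the first SOPS, their answers, or their willingness to return the form, could differ by arm. In a repeated-measures analysis, a baseline shift confined to one arm enters the group-by-time contrast in full.

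**Working it through.** **1. The two statements side by side.**

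| | Randomization | Phases of study |
|---|---|---|
| Unit assigned | tutor-resident pair | tutor-resident pair |
| Method | random, stratified by teaching unit | simple random sample |
| Balance promised | equal numbers; similar by centre and area | none stated |

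Both describe the assignment of the same pairs to the same two groups, so they cannot be two separate steps.

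**2. What a simple random draw does to unit balance.**

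Inputs: 69 pairs, arms of 35 and 34, seven units (Population section). Assumption: unit sizes 10, 10, 10, 10, 10, 10, 9 (69/7 ≈ 9.9), because the article gives none. A unit counts as badly split at 8:2 or worse; for the unit of nine this means 8:1 or worse, since 7:2 (78%) is less extreme than 8:2 (80%).

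*(a) Independent tosses.* For a unit of 10, 912 of the 1,024 outcomes are better than 8:2, so P(8:2 or worse) = 112/1,024 = 0.109. For the unit of nine, 492 of 512 are better than 8:1, so P(8:1 or worse) = 20/512 = 0.039.

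P(at least one unit) = 1 − (912/1,024)^6 × (492/512) = 1 − 0.499 × 0.961 = 0.52.

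*(b) Totals fixed, 35 of 69 drawn without replacement.* Units are then dependent. Count the draws of 35 in which no unit is badly split and divide by C(69,35). The exact count gives 1 − 0.594 = 0.406, about 41%. A simulation of 100,000 draws gave 0.404.

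*(c) A milder threshold.* At least one unit at 7:3 or worse (7:2 in the unit of nine): about 88% with totals fixed and about 93% with independent tosses.

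*(d) Stratified allocation for comparison.* With permuted allocation inside units, each unit of 10 can be held at 5:5 and the unit of nine at 5:4. This gives 6 × 5 + 5 = 35 and 6 × 5 + 4 = 34, the planned arms.

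**3. The overall split.** With independent tosses, a 35/34 split has probability 2 × C(69,34)/2^69 = 0.19. With a draw of 35 from 69 it is certain. The planned 35/34 therefore agrees with a stratified allocation or a fixed-size simple draw, and does not show which was used.

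**4. Timing.** Assignment is in the first quarter and the baseline SOPS in the second. The article says nowhere when participants learned their arm. The possible effect on the baseline can be described but not sized from this document.

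**The case against.** The strongest reply is that this is a reporting inconsistency with modest consequences. Unstratified random allocation gives an unbiased comparison in expectation; chance imbalance by unit costs precision and face balance, not validity. That stands. So does the caution that the percentages rest on assumed unit sizes. One could also read the simple random sample loosely as a random draw within units, but the Phases of study section does not say so.

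A reader might go further in three ways that the document does not support:

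- *That the baseline is biased.* Drawing up the list before the baseline does not by itself bias it. Participants must also know their arm, and the article neither states nor excludes this. Any figure for the size of such a bias would be invented.
- *That pairs were invited into known arms.* The Population section says "we will request the participation of 35 tutors and 35 residents in the intervention group", which can be read that way. It can equally be a statement of planned arm sizes: the Randomization section invites every pair in Galicia, and the Phases of study section describes the consent letter before it describes assignment.
- *That the stratified account is the true one and the other a slip.* The Phases of study section is largely in the past tense and may record what was done. Changing it without checking could misreport the trial.

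The past tense also limits the remedy. The article describes dissemination as the present phase, so the calendar may no longer be open to change.

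**Conclusion.** The contradiction is real and has to be resolved: the article states two different methods for one allocation step. If a simple random sample was used, the allocation is valid but the claimed balance by teaching unit was not secured. Under near-equal unit sizes, at least one unit is split 8:2 or worse in about 41% (totals fixed) to 52% (independent tosses) of draws. Other unit sizes would change these figures, but simple allocation would still not guarantee balance by unit.

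The order of allocation and baseline is a secondary point. It matters only if arms were disclosed before the first SOPS was returned; the article leaves that open, so an unbiased baseline is not assured, but bias is not shown.

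**What to change.** 1. **State one method in both sections**, after checking the allocation record.
   - *If stratified by teaching unit:* correct the sentence in Phases of study. Say how equal numbers are obtained within units, for example by permuted blocks from a computer list with no manual balancing; the present wording about taking special care names no mechanism. Include teaching unit as a factor in the analysis.
   - *If a simple random sample:* withdraw the claim in the Randomization section that stratification makes the groups equivalent, and say whether the totals were fixed at 35/34.
2. **Deal with the order of allocation and baseline.**
   - *Where still possible:* allocate, or at least disclose the arm, only after the baseline SOPS has been returned. The small downside is that workshop invitations go out later.
   - *Otherwise:* state when participants learned their arm, report baseline return by arm, and interpret the pre-post change accordingly.

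The cost is a few sentences and one check of the allocation record. A factor for unit uses six degrees of freedom (7 − 1), which is affordable with 69 pairs.

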## Discussion

In our analysis of this research, we have encountered certain difficulties that were evaluated in a realistic manner before initiating execution of the project.

Although a number of tools have been developed to assess organizational culture [38], these tend to measure a large number of dimensions without focusing specifically on patient safety [39]. However, surveys centered on patient safety culture have appeared [40], as have reviews of these surveys [23].

The psychometric properties and dimensionality of the AHRQ questionnaire have recently been reviewed by Sorra and Dyer [39] with a survey among 331 hospitals, 2267 hospital services and 50513 survey respondents. The results support the 12 dimensions and 42 themes included in the SOPS, with psychometric properties acceptable at all levels of analysis, with few exceptions.

Although other instruments are available for measuring the safety environment, the one elaborated by the AHRQ was chosen owing to its rigorous process of construction and validation [41], with psychometric properties confirmed in the version adapted in Spanish (Analysis of Patient Safety Culture in Hospitals of the Spanish National Health System [*Análisis de la cultura sobre seguridad del paciente en el ámbito hospitalario del Sistema Nacional de Salud español*] [42] and with extensive experience of application in the United States [43].

It is possible that SOPS, even if it is initially oriented to both hospital and non-hospital environments and culturally validated for a Spanish setting, may not faithfully reflect the characteristics of primary care in our region. Thus, difficulties may arise in the reading and interpretation of items and dimensions. Nevertheless, adaptation to this care level is an important step forwards in patient safety culture, which is less developed and studied at this care level.

APEAS questionnaire was proposed for the registration of adverse events, being the only state-wide used in Spain, allowing us to compare the results. It does not correspond to the taxonomy currently proposed by WHO [44-46], that was later published.

Specialized training in family and community medicine in Spain is conducted through the MIR system (MIR is Spanish for resident internal doctor), and access to it is by means of a competitive exam and a standard that measures candidates' academic transcripts and ranks them by scores composed of the sum of the exam grade and the transcript grades, whereby candidates can select their field of study as per this order. For every specialized field-including, of course, family medicine-there is a national commission that establishes the curriculum of study, the MIR requirements, certification of educational institutions and units, quality control of the structure, process and results, among others.

The most recent family medicine curriculum in Spain was approved in 2005. It is a highly ambitious, quite complete and detailed program that sets out each objective according to an order of priority within each defined skill area. Training is distributed among the 4 years planned in rotations through different hospitals and the health center for the initial 6 months and the last year of residence. In family medicine, unlike other hospital specializations, each resident has an assigned tutor in the health center work alongside them through their residence and supervise the fulfilment of objectives as part of a learning evaluation that identifies possibilities for improvement and proposes corrective measures, with constant feedback in continued active tutoring meetings.

One of the significant advances and strengths of this pioneering program is the implementation of learning evaluation through the completion of a reflective practice guide, in which residents think about the tools being used and the tutors supervise the method.

As per the training calendar of family MIR, this study should closely match the established timetable, as residents in family medicine will be in the health center for 1 year before completing their training, and then they will disperse. Thus, the performance period is limited by the difficulty caused by the need to re-establish contact with residents once their training is over. This demands significant discipline and dedication, as a multicenter study with substantial distances between participating centers makes coordination particularly arduous, a factor to be taken into account when considering the obstacles to be overcome.

The inherent characteristics of primary care in Spain, where the accessibility of care is foremost, exert special pressure on medical professionals, as they have little control over the distribution of daily work, with the subsequent conflicts of space and time for the inclusion of research work. Therefore, this difficulty in managing and organizing work constitutes a major barrier to the execution of any kind of research and, in the best of cases, proves to be a special burden no matter how small the tasks may be.

## List Of Abbreviations

AE**: **Adverse Events; AHRQ**: **Agency for Healthcare Research and Quality; AIDS**: **Acquired Immunodeficiency Syndrome; APEAS**: **Study on Patient Safety in Primary Health Care; ENEAS**: **National Study on Adverse Effects Linked to Hospitalization; GDP**: **Gross Domestic Product; IOM**: **Institute of Medicine; MIR**-**4**: **Training doctors in the 4th year of family medicine; MSPS**: **Ministry of Public Health and Social Affairs; PC**: **Primary care; PPP**: **Purchasing Power Parity; SOPS**: **Hospital Survey on Patient Safety Culture; WHO**: **World Health Organization

## Definitions

Adverse event

Set of incidents and adverse effects.

Adverse effect

Any unforeseen and unexpected accident identified upon medical examination that has caused an injury and/or incapacity due to health care received and not the patient's base ailment. To determine whether the adverse event is due to care, reviewers score on a scale of 6 points (1 = no evidence or little evidence; 6 = practically certain evidence) their degree of confidence that the AE is due to health care and not the pathological process. A priori, we would use a cut-off point of ≥ 2 to consider it to be positive.

Avoidable adverse effect

To determine whether the adverse event is avoidable, reviewers will score on a scale of 6 points (1 = no evidence or little evidence; 6 = practically certain evidence) their degree of confidence that the adverse effect is avoidable. A cut-off point of ≥ 4 is used to consider it to be positive. Determinations: AE frequency. Proportion of avoidable AEs.

Grave adverse effect

Causing death, residual incapacity upon release or requiring surgery.

Moderate adverse effect

Causes hospital stay of at least 1 day or requires emergency or specialist care.

Mild adverse effect

Injury or complication that causes none of the above.

Incident

Unforeseen and unexpected random event that causes no harm to the patient. It can also be defined as an event that in different circumstances might have been an adverse event or an event leading to problems for the patient if not discovered or corrected in time.

Medical error

Mistake or omission in the practice of medical professionals that may contribute to the occurrence of an adverse event.

Drug error

Effect that can be avoided and which is caused by the improper use of a medication, causing harm to a patient while under the care of a medical professional, patient or consumer.

Adverse drug reaction

Alteration and/or lesion caused when medications are used appropriately.

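### The causation cut-off of 2 or more excludes only the lowest score, is looser than the avoidability cut-off on a like-anchored scale, and no reason is given

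*Protocol article*

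**What the plan says.** All the relevant rules are in the Definitions section of the protocol article.

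- **Concept.** An adverse effect is an injury or incapacity "due to health care received and not the patient's base ailment".
- **Scale.** To apply it, "reviewers score on a scale of 6 points (1 = no evidence or little evidence; 6 = practically certain evidence) their degree of confidence" in causation by care. Only points 1 and 6 carry wording; points 2 to 5 carry none.
- **Causation rule.** "A priori, we would use a cut-off point of ≥ 2 to consider it to be positive".
- **Avoidability rule.** The next definition uses a 6-point confidence scale with the same two anchors, but: "A cut-off point of ≥ 4 is used to consider it to be positive".
- **Figures to be produced.** "Determinations: AE frequency. Proportion of avoidable AEs".
- **Scope of an adverse event.** "Set of incidents and adverse effects". Incidents are defined separately as causing no harm.

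Under Data analysis, the only planned use of these records is that "a descriptive analysis of declared adverse events will be undertaken". Under Measurement of results, the dependent variable for the first hypothesis is safety culture measured by the SOPS, not AE frequency.

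**The concern.** The concept is categorical: the harm comes from care and not from the underlying disease. The working rule asks for very little. An injury one step above the bottom anchor, which stands for no or little evidence, is classed with one whose causation by care is practically certain.

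The avoidability rule makes this more noticeable. On a like-anchored scale the plan requires a score in the upper half before it calls an event avoidable, yet for causation it accepts every score but the lowest. An event scored 2 for causation and 4 for avoidability is therefore reported as an avoidable adverse effect of care, although confidence that care caused it was low.

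Both named determinations depend on the causation cut-off. It sets the adverse-effect part of AE frequency, and it sets which events form the denominator of the proportion avoidable. Readers are likely to take both figures as describing harm due to care, and nothing in the article tells them that the rule is a deliberately sensitive one.

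**Working it through.** The article gives no distribution of causation scores, so it contains no figure to reproduce. The check counts scale points, gives the ratio in general form, and then uses assumed distributions. The cut-off of 4 is a comparator taken from the plan's own avoidability rule.

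**1. Scale points called positive.** At 2 or more, points 2 to 6 are positive: 5 of 6. At 4 or more, points 4 to 6 are positive: 3 of 6. The difference is the events scored 2 or 3.

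**2. Ratio of adverse-effect counts.** Let f be the share of the adverse effects counted at 2 or more that score 2 or 3. The count at 4 or more is then (1 − f) times the count at 2 or more, so

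ratio = 1/(1 − f).

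Since f cannot be negative, the ratio is never below 1.

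| f (assumed) | Ratio |
|---|---|
| 0 | 1.00 |
| 0.20 | 1/0.80 = 1.25 |
| 0.40 | 1/0.60 = 1.67 |
| 0.50 | 1/0.50 = 2.00 |

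**3. Whole score distributions, all assumed.**

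| Shape of scores 1 to 6 | Positive at ≥ 2 | Positive at ≥ 4 | Ratio |
|---|---|---|---|
| Even across all six points | 83.3% | 50.0% | 1.67 |
| Mostly low (30, 25, 20, 12, 8, 5%) | 70% | 25% | 2.80 |
| Mostly high (5, 5, 10, 20, 25, 35%) | 95% | 80% | 1.19 |
| None at 2 or 3 (20, 0, 0, 20, 30, 30%) | 80% | 80% | 1.00 |

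The direction is fixed and the size is not: 1.00 to 2.80 over these four shapes.

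**4. Dilution by incidents.** The stated determination is AE frequency, and adverse events include harmless incidents. Suppose incidents are counted whatever the causation score. Take 100 adverse effects at 2 or more, of which 60 remain at 4 or more (f = 0.40), plus 100 incidents (assumed). The ratio for AE frequency is (100 + 100)/(60 + 100) = 200/160 = 1.25, against 1.67 for adverse effects alone. The article does not say whether incidents pass through the causation score.

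**5. Proportion avoidable.** Let a be the avoidable share among adverse effects scoring 2 or 3 for causation, and b the share among those scoring 4 or more. At 2 or more the proportion is f·a + (1 − f)·b; at 4 or more it is b. The difference is f·(a − b). Its sign depends on whether low-confidence events are judged avoidable more or less often than the others, and its absolute size cannot exceed f. This proportion may therefore move in either direction or not at all.

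**The case against.** The best defence is that the article states a concept and then an operational rule chosen in advance. A low threshold is a legitimate, sensitive way to capture possible harm. Causation and avoidability are different constructs, and nothing obliges a plan to use one threshold for both. This stands: the document does not show that 4 is the right causation cut-off, and a reader who infers that the rule contradicts the definition goes too far, because the two sentences can stand together.

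A reader might also infer that events scored 2 or 3 are ones the scorer thought more likely due to the disease. The document does not support that. The scale grades confidence and evidence, its middle points are unlabelled, and a 2 or 3 may mean limited evidence for care rather than evidence for the disease.

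Nor can inflation of the AE frequency be stated as fact. There is no reference value, every ratio above 1 rests on an assumed distribution, and the ratio may be exactly 1. Incidents may dilute the effect further.

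Two supporting arguments are also unavailable. The article does not state which cut-off the APEAS study used, so keeping 2 or more cannot be justified from this text as like-for-like. Additional file 2 is not shown, so it cannot be said that the form itself carries the 1 to 6 score. The section on feedback does not say that the cut-off is applied to what participants receive.

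Finally, a second-threshold table is the kind of detail often left to an analysis plan. That is true of the table, but the cut-off itself is fixed in this article. What remains is that the stated rule is lenient, differs from its neighbour without a reason, and feeds two named figures.

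**Conclusion.** The point holds as a minor one. The causation rule admits injuries for which confidence in causation by care is low, and it is looser, without explanation, than the avoidability rule on a scale with the same anchors. It is certain that the adverse-effect count at 2 or more is at least as high as at 4 or more. The size is unknown: a ratio of 1.0 if no counted event scores 2 or 3, 1.67 if 40% do and 2.0 if half do, less for AE frequency if incidents are counted regardless of score. The proportion avoidable may shift either way.

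The consequence is confined to a secondary descriptive result. The SOPS outcome, the sample size and the randomised comparison do not depend on this cut-off.

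**What to change.** 1. Keep 2 or more as the prespecified definition, label it as the sensitive one, and give in one sentence the reason it differs from the cut-off for avoidability.
2. In the descriptive analysis, also tabulate AE frequency and the proportion avoidable at a causation score of 4 or more, using the scores that the Definitions section already has reviewers give. Show adverse effects and incidents separately, so that the effect of the cut-off is not hidden in the total.
3. Base any statement that events were due to care on results that hold at the stricter cut-off.

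The cost is one extra table column and a sentence or two in the definitions. As long as the individual scores are kept and not only the positive or negative classification, no new data are needed. The downside is that the frequency at the stricter cut-off may be lower.
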